#### Aim 1: data analysis

For descriptive statistics, we will compute frequencies and percentages for each categorical variable and calculate means and standard deviations for continuous variables. Quantitative analyses will be performed in R 4.0.3 [60]. In collaboration with the Indiana University Center for Survey Research, the research team will review qualitative and quantitative responses to identify general patterns and main themes. The results of the survey analysis will be reviewed by the research team and considered for incorporation into future school surveys. Results from Aim 1 will be used to inform Aim 2 co-design session topics and to guide co-design session agendas.

Qualitative data from the co-design sessions will be analyzed through thematic analysis to identify unique community needs. To conduct this analysis, the team of researchers will complete six phases (familiarization with data, generation of codes, searching for themes, reviewing themes, defining and naming themes, and producing the report) as outlined by Braun and Clarke (2006). Quantitative data will be assessed using linear regression models to explore the relationships between key variables, with emphasis on physical activity levels, social media usage, and body satisfaction. For the linear regression models, model 1 will explore Body Satisfaction Prediction. The dependent variable will be body satisfaction (measured by the BSQ), and the independent variables will be body appreciation (BAS-2 scores) and body-guided behavior (MAIA-Y scores). The primary regressions will be: (Table 1).

**Table 1 Tab1:** Proposed regressions for analysis

Outcome	Independent Variables	Purpose
BSQ (Body Image Score)	MET, Sex	To assess the relationship between physical activity (MET) and sex on body image.
BSQ	BSMAS, Screen Time, Sex	To determine the impact of problematic social media use (BSMAS), screen time, and sex on body image.
BAS-2 (Body Appreciation)	MET, Sex	To explore the effect of physical activity and sex on body appreciation.
BAS-2	BSMAS, Screen Time, Sex	To analyze how social media use and screen time relate to body appreciation, accounting for sex.
BSQ	BAS-2, Sex	To evaluate the association between body appreciation and body image, adjusting for sex.
GAD (Anxiety)	Screen Time, BSMAS, Sex	To assess how screen time and social media use relate to anxiety, accounting for sex.
GAD	MET, Sex	To investigate the relationship between physical activity and anxiety, adjusting for sex.
MET	CAPL-2, Sex	To examine the effect of physical literacy (CAPL-2) and sex on physical activity levels (MET).
BSQ	CAPL-2, Sex	To determine the relationship between physical literacy and body image, adjusting for sex.
BAS-2	CAPL-2, Sex	To explore how physical literacy influences body appreciation, accounting for sex.

All models will use linear regression. For each model, we will report unstandardized beta coefficients, standard errors, 95% confidence intervals, and p-values. Variables will be checked for assumptions of linearity, normality, and multicollinearity prior to analysis

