## Background

Fifty-three percent of American girls are “unhappy with their bodies,” with 46% of 9–11-year-olds actively dieting and reporting body dissatisfaction (generally defined as a negative subjective evaluation of one’s body size, shape, or overall appearance) [1]. This body dissatisfaction is correlated with the development of life-threatening mental health issues (e.g., body dysmorphia, eating disorders, self-harm) [2, 3]. Body dissatisfaction in adolescence is associated with poorer quality of life [4] due to factors such as negative affect [5] and self-talk [6], as well as low self-esteem [7, 8] and self-acceptance [6].

Social media use during adolescence creates potentially serious complications for mental health. The use of social media during adolescence is linked to a significant 189% rise in U.S. hospital admissions for non-fatal self-harm among adolescent females, which has been correlated to increases in body dissatisfaction [9, 10]. Furthermore, there has been a more than 151% [11] increase in suicide rates among adolescent females, and this is associated with the rising trend of increased social media use [12].

Social media significantly impacts adolescent female body image, creating unrealistic appearances through edited images and messages [13–18]. Key issues include exposure to distorted self-images, prolonged exposure to edited content, and unrealistic body portrayals [17, 19, 20]. Importantly, the daily average of screen time for adolescents is 6 to 9 h, and more screen time is correlated with greater body dissatisfaction [21, 22]. Furthermore, age significantly influences the relationship between social media use and body satisfaction, as highlighted in a recent systematic review [23], with younger females being at greater risk of body dissatisfaction due to social media.

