### Aim 1 (needs assessment): assess adolescent females’ views on social media, physical activity, and factors impacting positive body image in the community

#### Aim 1: design

The study’s initial phase involves conducting a community-engaged research needs assessment (ORBIT Phase Ia) to identify the needs, goals, opportunities, and assets related to physical activity within the community. This phase aims to build on existing knowledge about the population-level effects of social media on psychosocial factors by gaining a detailed understanding of how these factors impact needs in rural populations. To achieve this, we will perform a comprehensive needs assessment focused on body image by surveying adolescents, parents, teachers, and school administrators. The survey will utilize a multilevel design that addresses individual, interpersonal, and community-level influences. The insights gained from this needs assessment will provide a foundational understanding of the interactions between social media, physical activity, and body satisfaction within the current school setting. Additionally, this assessment will inform future evaluations across additional school partners, enhancing the overall understanding of these dynamics in rural contexts.

AIM 1 will be conducted in one rural public school district in Indiana, including both the middle school and high school campuses. These schools serve students in grades 6 through 12 and are located in an under-resourced, predominantly White community where all students qualify for free and reduced-price meals. While we will not stratify recruitment by grade, we will aim to include students from each eligible grade level (6th–9th) to capture a range of developmental perspectives. Grade-level representation will be monitored during enrollment, and descriptive analyses will examine potential differences by grade to inform future iterations of the program. Recruitment is conducted in collaboration with school staff and includes multiple strategies to reach eligible students and parents. For students, in-school announcements and classroom visits by research staff are used to explain the study and distribute take-home flyers. Parents are informed through printed flyers sent home with students and direct communication facilitated by teachers or school administrators.

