#### Aim 3: data analysis

##### Quantitative analysis of survey measures

In our analysis process, we will begin by reviewing the completeness and distributions of all variables. If any variables demonstrate non-normal distributions, we will apply normalizing transformations as required. Internal consistencies of scaled scores will be evaluated using Cronbach’s alpha to ensure reliability.

This study’s primary objective is to evaluate the intervention’s feasibility using the following indicators: Feasibility of Intervention Measure (FIM), Acceptability of Intervention Measure (AIM), Intervention Appropriateness Measure (IAM), attendance, and retention. Descriptive statistics—including means, standard deviations, and proportions—will be used to summarize these outcomes. A priori thresholds for success will be defined as a mean score of ≥ 16 out of 20 on the FIM, AIM, and IAM, representing a “good” rating. Attendance and retention rates will also be reported as proportions, with retention thresholds aligned with a minimum of 85% as an acceptable benchmark.

Secondary outcomes (e.g., body satisfaction and social media literacy) and exploratory outcomes (e.g., body appreciation and physical literacy) will be analyzed by assessing changes from pre- to post-intervention using paired-sample *t*-tests. Repeated measures ANOVAs will be used to further examine time effects and potential interactions. Age and BMI will be included as covariates in these models to enhance interpretation of between- and within-group differences.

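### None of the Aim 1 regressions includes age or grade, so their associations may be confounded by age and the social media models may average over different age-specific associations

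*Protocol article*

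**What the plan says.** Under *Aim 1: data analysis* the protocol describes a model 1 with BSQ as the outcome, in which "the independent variables will be body appreciation (BAS-2 scores) and body-guided behavior (MAIA-Y scores"). It then states "The primary regressions will be: (Table 1") and lists ten models with every independent variable named. Sex is in all ten rows. Age and grade are in none. Model 1 in the text has neither sex nor age.

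Row 2 (BSQ on BSMAS, screen time and sex) is there "To determine the impact of problematic social media use (BSMAS), screen time, and sex on body image". Row 4 has the same predictors with BAS-2 as the outcome. The last row is "To explore how physical literacy influences body appreciation, accounting for sex".

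Other sections bear on age:

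- *Background*: "age significantly influences the relationship between social media use and body satisfaction", "with younger females being at greater risk of body dissatisfaction due to social media".
- *Aim 1: design*: recruitment is not stratified by grade, each of grades 6 to 9 is to be represented, grade is monitored at enrolment, and "descriptive analyses will examine potential differences by grade to inform future iterations of the program".
- *Aim 3, Quantitative analysis of survey measures*: "Age and BMI will be included as covariates in these models".

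Aim 1 results are to inform the topics and guide the agendas of the Aim 2 co-design sessions.

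**The concern.** The sample deliberately spans several years of development. The *Aim 2: sample size calculation* section puts grades 6 to 9 at about 11 to 15 years. If screen time, physical activity or physical literacy shifts with age, and body image or anxiety does too, a model without age can report an age trend as an association with the exposure. Separately, if the social media association differs by age, as the Background says, a single pooled coefficient hides that difference.

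The covariates are written out model by model, so the omission is a stated choice and not a detail left to an analysis plan. Grade is an eligibility criterion and is monitored, so it is available for every child. At stake is whether the associations passed to the co-design groups reflect the exposures or partly reflect age.

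**Working it through.** **Count.** Table 1 has ten rows: BSQ four times, BAS-2 three times, GAD twice and MET once (4 + 3 + 2 + 1 = 10). Sex appears in 10 of 10, age or grade in 0 of 10. The Background statement concerns social media and body satisfaction, so it bears directly on rows 2 and 4. For the other eight rows the case rests on general plausibility.

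**Modification and confounding are separate.** In standard-deviation units, the slope bias from leaving age out is approximately

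bias ≈ (exposure–age correlation) × (effect of age on outcome).

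The documents give neither quantity, so both are assumptions. Large-sample simulation with a true slope of 0.30:

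| Exposure–age correlation | Age effect | Age × exposure | Slope without age | Slope with age |
|---|---|---|---|---|
| 0 | 0.3 | 0.2 | 0.30 | 0.30 |
| 0.3 | 0 | 0.2 | 0.30 | 0.30 |
| 0.3 | 0.3 | 0 | 0.39 | 0.30 |

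Modification alone (first two lines) does not bias the average slope. Confounding (third line) does, by 0.3 × 0.3 = 0.09. When both inputs range from 0.1 to 0.5, the bias runs from 0.1 × 0.1 = 0.01 to 0.5 × 0.5 = 0.25.

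**False positives.** The setting has no true exposure effect, one exposure plus sex in the model, a two-sided 5% test, and the same correlation r of age with exposure and with outcome. The spurious standardised slope is r².

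| r (assumed) | Spurious slope | N = 50, no age term | N = 30, no age term |
|---|---|---|---|
| 0.1 | 0.01 | about 5% | about 5% |
| 0.2 | 0.04 | about 6% | 5–6% |
| 0.3 | 0.09 | 9–10% | about 7.5% |
| 0.4 | 0.16 | about 20% | about 13% |
| 0.5 | 0.25 | about 42% | about 26% |

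With age in the model the rate is about 5% throughout. Both sample sizes are shown because *Aim 1: setting and sample* plans 50 students and *Aim 1: sample size* plans 30 or more.

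**Cost in power.** *Aim 1: sample size* gives an effect size of 0.6, three predictors and alpha 0.05, with 29 participants required and no power stated. Reading 0.6 as f², the overall F test (noncentrality f² × N, degrees of freedom k and N − k − 1) needs N = 23, 28 or 33 for 80%, 90% or 95% power with k = 3. The stated 29 is close to the 90% figure, but without a stated power it cannot be reproduced uniquely. The point does not rest on it. On the same basis:

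| Predictors in the model | Power, N = 30 | Power, N = 50 |
|---|---|---|
| 3 (as planned) | 0.925 | 0.997 |
| 4 (age added) | 0.889 | 0.994 |
| 6 (age and its interactions with BSMAS and screen time) | 0.807 | 0.984 |

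**The case against.** The strongest reply is that the Background describes effect modification, which does not establish confounding. Confounding needs age to be related to both exposure and outcome within grades 6 to 9, and no section says so or gives a figure. That stands: a reader might infer that the Aim 1 associations *are* confounded by age, and the documents do not support this.

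It also stands that the Background statement reaches only rows 2 and 4, and that harm is near nil at correlations of 0.1 to 0.2. The regressions are described as exploratory. Their results inform co-design alongside qualitative responses and discussion, so no regression alone sets the agenda.

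The Aim 3 comparison is only supportive. Those models concern change over time, and age and BMI are included there to aid interpretation, so leaving age out of Aim 1 is not a contradiction.

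The planned descriptive analyses by grade are a partial safeguard. They may reveal grade differences, but they adjust no Table 1 coefficient, and their stated use is future iterations of the program. None of this gives a reason to omit a variable that is already recorded.

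**Conclusion.** The point holds as a possibility that the plan leaves open without need. All ten primary regressions and the text's model 1 omit age and grade. The Aim 1 associations may therefore be confounded by age, and rows 2 and 4 may average over associations that differ by age. The case is strongest for those two rows.

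The size cannot be determined from the documents. Under the stated assumptions the effect on false positives is negligible up to correlations of about 0.2 and material from about 0.3. The 42% figure needs age to correlate 0.5 with both variables, which nothing in the protocol indicates.

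The wording adds to the problem. Four Purpose entries (rows 2, 3, 8 and 10) speak of impact, effect or influence, which cross-sectional models adjusted only for sex, and in row 2 for the other social media measure, cannot support. The change is worth making because it is cheap, not because bias has been shown.

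**What to change.** 1. Add age, or grade as a linear term, to the Table 1 models and to the text's model 1. The social media models come first.
2. An age main effect deals with confounding but not with the modification the Background describes. For rows 2 and 4, also show the associations by grade or with an exploratory age-by-exposure term, labelled as exploratory given the sample size.
3. In the four Purpose entries that use *impact*, *effect* or *influences*, write *association*.
4. Keep the descriptive results by grade.

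The main-effect change costs one degree of freedom and no new data collection. For a three-predictor model with 0.6 read as f², overall-test power falls from about 0.997 to 0.994 at N = 50, and from 0.925 to 0.889 at N = 30. Interaction terms cost more, so if recruitment ends near 30, results by grade or an interaction should be presented as descriptive only.

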### Aim 2: Co-create the Hoosier Sport Re-Social intervention in collaboration with White River Valley middle school children and adults

#### Aim 2: design

The study’s second aim is to co-design a prototype intervention and implementation protocol for Hoosier Sport re-social (ORBIT Phase Ia). Aim 2 will yield a protocol for both an intervention and implementation strategy. From here forward, “intervention protocol” will be used to describe the inclusive document detailing intervention components and implementation components (see Fig. 2 for more details). This phase aims to gain greater comprehension of the body satisfaction-based needs of youth from primarily low-socioeconomic rural backgrounds by focusing on individual, interpersonal, and school-level influences. The process will follow an established 5-step participatory co-design protocol [61, 62], consisting of sessions dedicated to problem identification, solution generation, solution evaluation, operationalization, and prototype evaluation. This participatory approach aims to empower both children and adults (e.g., parents [*n* = 3] teachers [*n* = 2]) to contribute to designing the *Hoosier Sport Re-Social* body-positivity intervention protocol. We plan to recruit two separate co-design teams, each comprised of *n* = 5 adults and *n* = 5 adolescents. The completion of these participatory co-design sessions will culminate in a testable prototype intervention and implementation protocol to be tested in Aim 3.

#### Aim 2: setting and sample

We plan to form two co-designer groups, one comprised of parents and the other children, with each group consisting of *n* = 5 recommended group size for participatory design [63]. This odd number of participants allows for a majority vote to resolve ties between design alternatives within the group. Recruitment of adults and children will occur through parent/guardian meetings and school administrators’ weekly newsletters. While utilizing convenience sampling due to limited sample size and time constraints, efforts will be made to enroll an approximately equal distribution of 50% female and 50% male participants, including those regularly involved in social media and those who are not. To be eligible for participation, children must be enrolled in middle or high school, entering 6th to 9th grade, and have parental consent while committing to attend all 5 co-design sessions. Adults eligible for inclusion must be a parent/guardian of a current 6th through 9th-grade student at the school and be willing to attend all 5 co-design sessions.

#### Aim 2: procedure

The two design teams will engage in a series of five co-design sessions spread across 3 months, with approximately 2 weeks between sessions. The adolescent group will initiate the process, while in parallel, the adult group will alternate sessions with the adolescent group (e.g., adolescent session, adult session, and so forth). The adult group will collaborate with the study team to review and refine the prototype developed by the children, aiming to retain as many adolescent-derived components as possible. This simultaneous yet alternating co-design approach empowers adolescents to incorporate essential concepts such as fun and enjoyment, while allowing adults to refine the intervention protocol for feasibility and practicality. Please see Fig. 4 for additional details.

**Fig. 4 Fig4:**
[figure not shown]
Co-design session goals

Facilitated by an experienced team member trained in group coaching and discussions, each session will be guided by open-ended questions aligned with specific session goals. For instance, the first session will focus on understanding challenges related to adolescent body image behaviors. The iterative design process involves collectively understanding challenges, generating various solution ideas, and progressively developing a detailed intervention protocol. The facilitator will encourage discussion, interpretation, and respectful debate among team members while ensuring progress. Insights from Aim 1’s body image-related needs, goals, opportunities, and assets will be integrated into discussions by sharing survey results with co-designers.

The research team will collect observation notes and audio recordings to analyze the design teams’ collaborative efforts. These records will capture participants’ conversations, thought processes, and collaborative endeavors in generating and grouping intervention design solutions. Facilitators will guide participants in generating and collaborating on intervention protocol design solutions. Each session will last 60–75 min, and observation notes will be analyzed alongside audio recordings. In the final session, teams will evaluate the feasibility, acceptability, and appropriateness of the prototype Hoosier Sport Re-Social protocol using adapted measures tailored to our study context, namely the Feasibility of Intervention Measure (FIM), Acceptability of Intervention Measure (AIM), and Intervention Appropriateness Measure (IAM) described in subsequent sections [64].

#### Aim 2: measures

The Feasibility of Intervention Measure (FIM), Acceptability of Intervention Measure (AIM), and Intervention Appropriateness Measure (IAM) are concise four-item assessments used to gauge implementation outcomes, serving as indicators of implementation success [64, 65]. These measures are instrumental in prospectively evaluating stakeholders’ perceptions regarding the feasibility, acceptability, and appropriateness of *Hoosier Sport Re-Social*. The FIM, AIM, and IAM have demonstrated robust psychometric properties, including content validity, discriminant content validity, reliability, structural validity, structural invariance, and responsiveness to change [64].

#### Aim 2: sample size calculation

To ensure a robust and effective co-design process, our teams will consist of faculty and student researchers (*n* = 6) collaborating with either adolescents (*n* = 5) or adults (parents, teachers) (*n* = 5) from the middle/high school community. Specifically targeting 6th–9th grade female students, generally aged 11 to 15 years. The composition of our teams reflects the unique expertise within our research group. The deliberate odd number of participants (totaling 13) serves a strategic purpose in facilitating decision-making processes during co-design sessions. This odd number ensures the possibility of a clear majority vote, which becomes instrumental in resolving potential ties when choosing between different design alternatives within the collaborative group. This thoughtful consideration of team composition and participant count underscores our commitment to fostering a productive and inclusive co-design environment for meaningful engagement and decision-making within the middle/high school community.

#### Aim 2: data analysis

The study will use inductive thematic analysis to analyze qualitative data from semi-structured interviews, aiming to gain insights directly from participants. This analysis involves identifying emerging patterns and themes without imposing predefined categories. Interviews will be transcribed verbatim, followed by an iterative coding process to identify meaningful units and group them into preliminary themes. Themes will be refined through team discussions to ensure accuracy and reliability. Inter-coder reliability will be established by multiple researchers coding a subset of interviews. The final thematic framework will offer a nuanced understanding of participants’ perspectives, informing recommendations crucial for the project’s outcomes. This analysis will serve as a robust basis for evidence-based conclusions and guide the project's direction.

Additionally, we will utilize descriptive statistics to analyze quantitative data derived from the Feasibility of Intervention Measure (FIM), Acceptability of Intervention Measure (AIM), and Intervention Appropriateness Measure (IAM) employed in session 5. To ensure a thorough assessment, we will establish clear criteria for evaluating the success of each feasibility aspect (a mean score of ≥ 16/20). Specifically, for the FIM, success will be determined by meeting a predefined threshold of participant engagement and adherence rates. For the AIM, we will gauge success based on whether participant satisfaction scores meet or exceed established benchmarks, indicating the intervention’s acceptability. The IAM will be evaluated by determining if the majority of participants consider the intervention appropriate based on predefined indicators of suitability and relevance. By the conclusion of session 5’s analysis, we will have a comprehensive draft of the intervention protocol prepared for piloting and feasibility testing in Aim 3. This draft will be informed by the results and success metrics from these measures, ensuring that the protocol is both feasible and well-received.

